## Methods

2

### Study setting

2.1

The study presented here is one of two additional studies accompanying the main Res@t study (32). It is carried out by the University Medical Centre Rostock and will be conducted in the urban area of Rostock and the district of Rostock (approx. 200 and 220 thousand inhabitants) in the German state of Mecklenburg-Western Pomerania. We are planning recruitment for the period from May 2024 (first participant in) to March 2025 (last participant in). The study presented here takes an approach, where child and youth welfare providers identify adolescents who are at particularly high risk for DMUD. We expect this group to be low on motivation, calling for a more blended approach wherein extended face to face contacts are necessary to maintain compliance.

### Eligibility criteria

2.2

Inclusion criteria for participants:

- Recipients of or the recommendation to receive child or youth welfare or have special needs for schooling.- 10 to 19 years of age (WHO definition of adolescence).- Cut-off for disordered or hazardous media use in the Gaming Disorder Scale for Adolescents/for Parents (GADIS-A/-P), Social Media Disorder Scale for Adolescents/for Parents (SOMEDIS-A/-P) and Streaming Disorder Scale for Adolescents/for Parents (STREDIS-A/-P) is reached (see primary outcome).- Fulfilled criteria for disordered or hazardous media use according to ICD-11 criteria (6C51, 6C5Y, QE22, QE2Y).- Written informed consent is given (for adolescents under the age of 16, the informed consent of the legal guardian is also necessary).

Or

- Are a parent/legal guardian of a participant fulfilling the criteria above.Exclusion criteria for participants:- Acute severe psychiatric disorders with a symptom burden that prevents participation in the study (i. e. psychotic disorders or disorders due to substance use).- Pervasive developmental disorders (i. e. autism spectrum disorder).- Acute suicidality.- Inability to understand the study instructions (i. e. severe disorders of speech or language, diminished intelligence or lack of german language skills).

### Recruitment

2.3

Access to the sample is mainly via the employees of child and youth welfare services and facilities. They establish contact between potential participants and our study team. As soon as contact has been established, the study team takes on all tasks relevant to the study and the employees of the child and youth welfare services have no further obligations. Furthermore, recruitment takes place in the district and meeting centres of the city of Rostock, as these are places that are frequented by adolescents from problematic backgrounds on the one hand and are accompanied by child and youth welfare staff in these facilities on the other. Finally, the work groups on child and adolescent psychiatry and addiction disorders in the city and district of Rostock are also included by the corresponding psychiatry coordinators and potential participants who are in child and youth welfare services are recruited. Once the study team has received the contact details of willing participants from the youth and social services, the participants and legal guardians provide informed consent to the study team. The study team then administers questionnaires at all-time points (screening, baseline, interim, post-intervention, follow-up 1 and 2) and conducts the clinical interviews (baseline and post-intervention).

### Intervention

2.4

The IG receives the app-based resource-strengthening adolescent and parent training programme (Res@t digital) after completing baseline assessment. The training consists of 10 modules: a first week training start following two weeks of psychoeducation, five weeks of specific contents, a one week relapse prevention and finally a booster session. A new module is activated every week, whereby the booster module is only activated 5 weeks after module 9 in week 15 of the training. The specific contents differ for adolescents (Res@t-A) and parents (Res@t-P), with the exception of the module on communication. Adolescents receive modules with specific contents on health and sleep hygiene, self-care, dealing with emotions and social relationships, while parents receive modules on developmental tasks and parenting styles, implementing rules, applying rules and family health. Depending on the type of dominant DMUD or hazardous use pattern, the content of the app is adapted to it. In addition, participants can use a diary in which they can enter daily times of media use, mood, activities, daily structure and sleeping times. For a detailed description of the training and the app contents, see Paschke et al. (32). Participation by parents is encouraged but not mandatory. Participants in the CG are assessed in the same way as in the IG using questionnaires and EEG (see outcomes below), but receive Res@t-A/P only after completing the last assessment and on an optional basis.

### Outcomes

2.5

#### Primary outcome

2.5.1

The primary outcome is the difference in the severity of specific DMUD or hazardous use pattern between IG and CG within 20 weeks of enrolment, measured at 5 time points (screening, interim, post-intervention, follow-up 1 and 2) at 5-week intervals. It is assumed that the group using the app (IG) shows bigger decreases in DMUD or hazardous use pattern compared to the group without (CG). In the event that an individual shows more than one DMUD or hazardous use pattern, the severity is operationalised by the supervising study team with the most severe type of DMUD or hazardous use pattern (gaming, social media or streaming). In order to assess gaming, social media and streaming as key areas of digital media consumption, the GADIS-A/-P, SOMEDIS-A/-P and STREDIS-A/-P are used to identify disordered or hazardous media use (33–38). All three questionnaires are based on the ICD-11 criteria for gaming disorder and other specified disorders due to addictive behaviours, which are specified here as social media use disorder and streaming disorder. The questionnaires consist of 4 items cognitive-behavioural symptoms (CBS) of problematic media use, 5 items negative consequences (NC) and one item on the frequency of these difficulties, with the exception of STREDIS-A/-P, in which CBS and NC account for 3 and 6 items respectively. If the cut-offs for CBS and NC are reached and the time criterion is met, disordered media use is indicated. If only the cut-off for CBS is reached, but not for NC, hazardous media use is assumed. If only NC but no CBS is present, another mental disorder may be present. In addition, a clinical interview to diagnose the presence of disordered or hazardous media use according to ICD-11 is assessed (at Screening and Post-Intervention) by authorised personnel. In order to take the high-risk sample into account, the assessment times were set more closely compared to the main study (32) and the baseline, post-intervention and follow-up assessments were supplemented by a measurement with GADIS-A/P, SOMEDIS-A/P and STREDIS-A/P interim (5 weeks after baseline in the middle of training) and an additional follow-up (5 weeks after the end of training and 5 weeks before the original follow-up). The interval of the DMUD questionnaires is therefore shortened from every 10 weeks to every 5 weeks (see participant timeline).

#### Secondary outcomes

2.5.2

As for secondary outcomes we assume that the use of the app will have a beneficial influence on several observation-based constructs related to DMUD. For psychopathological symptoms of the adolescents and perceived stress by adolescents and parents we assume a bigger decrease for the IG. The Strengths and Difficulties Questionnaire (SDQ) measures the psychopathological symptom burden of adolescents using five items on each of five subscales: emotional symptoms, conduct problems, hyperactivity/inattention, peer relationships problems and prosocial behaviour (39–41). The self-assessment exists from 11 years of age and a parallel external assessment by parents from 4 years of age. A slightly age-adapted version is available for 18 year olds and older. Adolescents are asked about the last six months in the screening and about the last month in the post-intervention. Parents only complete the SDQ-f at screening and were also asked about the last six months. The perceived stress of adolescents and parents within the past month is assessed using the 10 items of the Perceived Stress Scale (PSS-10) (42, 43). Analogous to the Transactional Theory of Stress and Coping, the scales Perceived Helplessness (primary appraisal; assessment of the situation and its stressors) and Perceived Self-Efficacy (secondary appraisal; assessment of resources and coping strategies) are formed (44). The phrasing was slightly adapted for adolescents in this study. The PSS-10 is measured at pre- and post-intervention.

On the other hand, we expect a greater increase in the IG for family functioning, family communication and mindfulness in adolescents and parents as well as an increase in family self-efficacy and quality of life of the parents. Family functioning is assessed using the five items giving the questionnaire its name: Adaptability, Partnership, Growth, Affection and Resolve, referred to as Family APGAR (45, 46). The family communication scale (FCS) measures “the act of sharing ideas, participating in decision making, and expressing feelings among members as a family unit” through ten items by self-assessment (47–49). Family functioning and communication are self-assessed by adolescents and parents. Family self-efficacy in parenting is measured by parents in the questionnaire with the same name (Familiäre Selbstwirksamkeit [FSW]) using nine items (50). The Mindful Attention Awareness Scale (MAAS-5) measures mindfulness (a state of mind characterised by receptivity, in which the subject is able to observe their thoughts, feelings and surroundings non-judgementally, thereby being present in the moment) in five items in adolescents and parents (51, 52). The Ulm Quality of Life Inventory for Parents (ULQIE) is used to assess parents’ life satisfaction over the last seven days (53). The 29 items of the ULQIE are partially incorporated into the subscales of physical and daily functioning, satisfaction with family support, emotional strain due to the child’s illness, self-development and well-being. All of the above mentioned questionnaires are collected at baseline and post-intervention.

With regard to the stages of change, we expect that adolescents in both groups will initially be in the stages of precontemplation or contemplation. After the intervention, more adolescents in the intervention group should be in the action stage than in the control group. Moreover, the influence of adolescent motivation should be explored as these variables should be modelled as covariates of change in DMUD or hazardous use pattern. Based on Prochaska’s Transtheoretical Model of Change in Behaviour (29, 30), we identify the stage of behaviour change in adolescents by means of the questionnaire for the assessment of readiness to change (Fragebogen zur Erfassung der Veränderungsbereitschaf [FEVER]) (54). The scales Precontemplation, Contemplation, and Action, each with eight items, are collected through self-assessment at baseline and post-intervention by the adolescents. The Preparation and Maintenance stages are not included in the questionnaire, as these are practically less informative.

Further, we expect an increase in sleep quality and a decrease in sleepiness and severity of insomnia among adolescents. Adolescents self-assess their sleep quality through the nineteen items of the Pittsburgh Sleep Quality Index (PSQI), their sleepiness in eight items of the Epworth Sleepiness Scale for Children and Adolescents (ESS-CHAD), and their severity of insomnia in seven items of the Insomnia Severity Index (ISI) (55–59). The sleep quality assessed by the PSQI can be determined from a combination of 7 components: subjective quality, latency (time required to fall asleep), duration of sleep, efficiency (ratio between time in bed and actual sleep), disturbance, use of sleep medication, and daytime dysfunction (e.g. due to fatigue or low activity level). The PSQI and ESS-CHAD reflect assessments over the last four weeks, while the ISI reflects assessments within the last two weeks.

To measure neurophysiological characteristics of brain activity, an EEG is used. For this purpose, a resting-state EEG (rsEEG) with 5 minutes of eyes open and 5 minutes of eyes closed is recorded at the beginning, followed by approx. 6 minutes of an oddball paradigm. A 30-minute sequence of a favoured media related activity (e.g. gaming) follows. The EEG is therefore carried out in the participants’ homes using a mobile EEG. The EEG ends with another rsEEG identical to the one at the beginning of the recording (see **Figure 1**). 45 minutes are planned for the preparation of a 32-channel montage. The oddball task is active visual and administered as described in Kappenman et al. (60). Participants are presented with the letters A, B, C, D and E in random order in a trial. In each block, one of these letters is defined as a target, which must be distinguished from the nontargets by pressing the up and down arrow keys using the dominant hand. There are a total of 5 blocks, each with 40 trials, in which each letter is presented 8 times. Each stimulus is presented for 200 ms and the inter-stimulus interval is 1,200 to 1,400 ms. The first EEG is carried out in the period from screening to the start of training and a further EEG after the end of training.

**Figure 1 f1:**
[figure not shown]
Procedure for the EEG assessment. rsEEG, resting-state EEG.

There is already a modest number of EEG studies that investigate neurophysiological measures of DMUD in the EEG and qualify as potential biomarkers of DMUD and its therapy response (61, 62). As these studies showed, people with IGD exhibit reduced power in the beta frequency band and increased power in the lower frequency bands of delta and theta in the rsEEG. In addition, a hyperconnectivity of the default mode network (DMN) and reward/salience network (RSN) appeared in the rsEEG of IGD subjects (63). In the domain of ERPs, the components of N2 and P3 showed increased negativity and positivity as markers of IGD (64, 65). Therefore we assume several EEG parameters to be associated to the intervention:

- Decreasing theta/beta-ratio in Power Spectral Density of

the rsEEG.

- Decreasing connectivity within the DMN and RSN.

- Decreasing negativity N2 in the oddball task.

- Decreasing positivity P3 in the oddball task.

#### Additional variables

2.5.3

Additional variables collected concern socio-demographic information, media rules, adolescent and parental media use, parental symptom burden and parenting style (66). Parental symptom burden is assessed at baseline by self-assessment of the nine items in the Patient Health Questionnaire (PHQ-9) for depressiveness and the seven items in the Generalizied Anxiety Disorder Scale (GAD-7) for anxiety within the last two weeks (67–70). Parents assess their parenting style in the Parenting Style Inventory (Eltern-Erziehungsstil-Inventar [EEI]) on the ten-item scales love, discipline, autonomy and on the seven-item additional scales cooperation with partners and cooperation with school, teachers and carers also at baseline (71). The religiosity scale is not surveyed. In addition, data on app usage behaviour is collected in regard to the number of app usage sessions, days, weeks, quests started, quests completed, mindfulness exercises observed, calendar entries, the relative completion of modules and the complete training.

### Sample size

2.6

Calculating the sample size for the primary outcome of the change in the severity of DMUD or hazardous use pattern between the intervention and control group over 5 measurement points is based on a mixed ANOVA with repeated measures and a within-between interaction. Assuming an effect size of 0.20, alpha error probability.05 and power.8, GPower 3.1.9.7 calculated a total sample size of 32 subjects with 16 per group. Due to the high-risk conditions of the target group, we assume a drop-out rate of 50%, which results in a total of 64 subjects to be recruited.

### Incentives

2.7

We expect the adolescents in our target sample of child and youth welfare programme to be less motivated than the participants from the clinical setting of the main study and are therefore pursuing a stronger and more consistent incentive strategy. Potential adolescent study participants already receive a €5 voucher for the screening, regardless of whether they will take part in the study or not. Adolescents receive €10 each for the complete baseline and post-intervention questionnaires and €5 each for the shorter GADIS/SOMEDIS/STREDIS-A questionnaires at interim, follow-up 1 and 2. The closer timing of the assessments results in a higher reward frequency.

### Assignment of interventions and blinding

2.8

Allocation to IG or CG is carried out by our consortium partner at the University Hospital Schleswig-Holstein Kiel, whose participants are randomised by ourselves in return. A computer-generated central randomisation list with variable block lengths, will be created by a project-independent employee of the Institute of Medical Biometry and Epidemiology at the University Medical Center Hamburg-Eppendorf. Since the CG does not receive any sham treatment and the randomisation as well as the installation and implementation of the app is coordinated by the study team, there is no blinding.

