Our trial aims to test the hypothesis of the superiority of Res@t digital combined with child and youth welfare service through a greater reduction in the symptoms of the most prominent DMUD or hazardous use pattern in the individual adolescent, compared to child and youth welfare service alone. Primary hypothesis: Res@t+TAU reduces symptoms of specific DMUD in adolescents compared with TAU alone, measured as a group-by-time interaction over 5 measurement points from screening to a 10-week follow-up. Secondary hypotheses: a) Res@t+TAU reduces symptoms of specific DMUD in adolescents as assessed by their parents compared with TAU alone, measured as a group-by-time interaction over 5 measurement points from screening to a 10-week follow-up. b) Res@t+TAU reduces symptoms of specific DMUD in adolescents assessed by authorised personnel compared with TAU alone, measured as change from screening to post-intervention. c) Res@t+TAU will have a beneficial influence on several observation-based constructs related to DMUD in adolescents (improved readiness to change and sleep quality), in parents (improved life satisfaction and family self-efficacy) and in both adolescents and parents (reduced stress levels and improved family functioning and mindfulness) compared with TAU alone, measured as change from baseline to post-intervention. d) Res@t+TAU reduces DMUD typical or potential markers in the EEG compared with TAU alone, measured as change from baseline to post-intervention.

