## Discussion

3

The Res@t digital intervention aims to close a gap in the treatment and care of adolescents with DMUD and their parents. The aim of this study is to test the effectiveness and efficacy of an evidence-based training programme for high-risk groups such as adolescents in child and youth services. In this kind of setting, the DMUD or hazardous use pattern is embedded in highly stressed adolescents and family members, whereby awareness of the problem and motivation for treatment as well as family support regarding the DMUD are likely to differ from adolescents who are undergoing primarily treatment. It is possible that the highly individual circumstances and conditions in which children and young people supported by youth and social services live may limit the generalisability of the findings on the usability and efficacy of Res@t digital. The same applies to the subsample concerning school-related difficulties. Nevertheless, the efficacy of Res@t digital will be further examined in the main study (32) of outpatients diagnosed with DMUD, recruited from psychotherapeutic and psychiatric practices and hospitals. To address the presumably harder-to-reach high-risk target group, we use a high dose of reinforcement in the form of gift cards every five weeks. It is hypothesised that this reinforcement system will be effective when used in conjunction with a blended approach, in which personal contact is intended to ensure the successful implementation of the intervention. Study staff will then support adolescents and parents with motivational barriers, technical issues, or organising app implementation. Combining digital and face-to-face components to address the various challenges of participation may be innovative, but not universally effective. For example, adolescents with high levels of stress or low motivation may benefit less from the digital component, or face-to-face contact may be a barrier for those who are socially averse. Furthermore, the lack of blinding in a waitlist design could lead to participants in the IG being influenced by expectations of their group allocation, leading to placebo effects and biased results. Participants in the CG could feel disadvantaged, which could change their perception and response to the use of digital media. In addition, the lack of intervention could lead to reduced adherence if participants feel inappropriately treated. Another limitation is the acquisition of neurophysiological parameters using EEG in the participants’ homes rather than under laboratory conditions. This results in a higher validity of the media use measures, but may lead to an overall lower reliability caused by environmental factors. Despite the limitations mentioned, a positively evaluated Res@t app can represent a low-threshold treatment option compared to outpatient and inpatient treatment and serve as a motivational tool to facilitate entry into further treatment in a therapeutic setting. The evaluation will also show whether the combination of Res@t digital with the blended approach and reinforcement strategies has the potential to be an effective treatment option for hard-to-reach adolescents at high-risk, underscoring the need for real people to accompany the digital.

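### Blinding is waived for every role, yet the stated reasons do not cover offline EEG processing; the unmasked post-intervention interview is neither mitigated nor listed as a limitation

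*Protocol article*

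**What the plan says.** Section 2.8 (Assignment of interventions and blinding) gives two reasons in one sentence. The first is "Since the CG does not receive any sham treatment". The second is that randomisation is coordinated by the study team and that "the installation and implementation of the app is coordinated by the study team, there is no blinding". No role is exempted.

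Two outcomes not reported by the family carry between-arm hypotheses in section 1.2:

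- **Hypothesis b**, symptoms "assessed by authorised personnel compared with TAU alone, measured as change from screening to post-intervention". Section 2.5.1 says that the interview "is assessed (at Screening and Post-Intervention) by authorised personnel", and section 2.3 says that the study team "conducts the clinical interviews (baseline and post-intervention").
- **Hypothesis d**, that the intervention "reduces DMUD typical or potential markers in the EEG compared with TAU alone, measured as change from baseline to post-intervention". Section 2.5.2 introduces the list of parameters with "Therefore we assume several EEG parameters to be associated to the intervention" and gives each a direction, always a decrease.

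Section 2.9 says that data are pseudonymised and that outcomes other than the primary are exploratory. Section 3 (Discussion) says that study staff help families with motivation, technical problems and use of the app. It notes that recording at home "may lead to an overall lower reliability caused by environmental factors". It discusses missing blinding as expectation in the intervention group and as disappointment and lower adherence in the control group.

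**The concern.** Families in a waitlist trial without a sham cannot be blinded, nor can the staff who install and support the app. That does not oblige the person who processes a stored EEG file to know its arm or visit. With a stated direction for every parameter and recordings that the article itself expects to be less reliable, knowledge of arm during processing is a source of bias that can be avoided.

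The interview is exposed in another way. The team that helps a family succeed with the app also rates whether the adolescent improved, and nothing in the article separates the two roles.

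At stake is how far these two outcomes can support the questionnaires, which are all open self- or parent-reports. The interview is the only between-arm rating not made by the family, and EEG is the only outcome other than a report or rating that carries a between-arm hypothesis.

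**Working it through.** The point rests on no figure in the plan. The main check compares each stated reason with each activity that the waiver covers.

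| Activity | Reason 1: no sham | Reason 2: team coordinates randomisation and app |
|---|---|---|
| Adolescent and parent questionnaires | applies | not needed |
| App installation and support | not needed | applies |
| Post-intervention interview | does not apply to the rater | applies as staffed, because section 2.3 makes the study team the interviewers |
| Offline EEG processing and scoring | does not apply | does not apply |

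The EEG row is the clear gap. Pseudonymisation (section 2.9) hides identity. It does not by itself hide arm or visit.

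**Which data are exposed.** The first interview is placed at screening or at baseline (sections 2.5.1 and 2.3 differ), before app training starts. The exposed rating is therefore the post-intervention one. For EEG, hypothesis d concerns change between two recordings. Either file may be processed after allocation is known, so both need coding, and the visit must be hidden as well as the arm.

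**The plan's sample size, for scale.** Inputs from section 2.6: effect size 0.20 (read as Cohen's f), alpha 0.05, power 0.80, two groups, five time points. Assumptions, not stated there: correlation 0.5 and sphericity (epsilon 1).

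- Noncentrality = f² × N × m / (1 − rho) = 0.04 × 32 × 5 / 0.5 = 12.8
- df1 = (2 − 1)(5 − 1) = 4 and df2 = (32 − 2)(5 − 1) = 120
- Power = 0.814, and 32 is the smallest even N that reaches 0.80
- Dropout: 32 / (1 − 0.5) = 64

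The plan's 32 and 64 reproduce. Masking changes neither.

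**Illustration of what a biased reading could do.** The documents give no size for such a bias, so a range is assumed. Let b be the differential between arms in SD units of the change score, with no true effect, a two-sided 0.05 test (the article sets no threshold for exploratory outcomes) and a normal approximation. With n per arm, SE = √(2/n), and the false-positive rate is 1 − Φ(1.96 − b/SE) + Φ(−1.96 − b/SE).

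Example with n = 16 and b = 0.2: SE = 0.354 and b/SE = 0.566, so the rate is 1 − Φ(1.394) + Φ(−2.526) = 8.7%.

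| Assumed b (SD) | 16 per arm (after 50% dropout) | 32 per arm (all recruited) |
|---|---|---|
| 0 | 5.0% | 5.0% |
| 0.1 | 5.9% | 6.9% |
| 0.2 | 8.7% | 12.6% |
| 0.3 | 13.6% | 22.4% |
| 0.5 | 29.3% | 51.6% |

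The figures are for one continuous score. They show sensitivity and do not estimate the bias in this trial.

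**The case against.** Several objections have force.

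- **The second reason does reach the interview.** A reader might infer that both reasons concern only participants and app installers. The study team does the interviewing, so as staffed the reason covers the rater too. This stands. The arrangement is a staffing choice, but the waiver is not unexplained there.
- **Masking the interview may not be cheap.** The article gives no staffing or cost figures, section 2.1 foresees extended personal contact, and an adolescent may reveal the arm. This stands. Low cost can be claimed only for coding the EEG files.
- **The EEG pipeline is not described.** Artefact handling, channel rejection and choice of windows are general knowledge of the method. The processing may be automated or fixed in a fuller document. This stands as a limit on the likely size of the bias, and the missing detail is no fault of an article. The waiver, however, is stated outright and names no exception for processing.
- **Masking does not remove expectation.** Participants know their arm while doing an active task at home, and a masked interviewer still hears answers from an unmasked adolescent. This stands.
- **The Discussion already admits possible bias from missing blinding.** It does, but only through participants, and says nothing of raters or EEG analysts.

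**Conclusion.** The point holds as a low-cost improvement to exploratory outcomes. The waiver in section 2.8 is wider than its reasons: it takes in offline EEG processing, to which neither reason applies. That affects the four parameter groups under hypothesis d. The post-intervention rating under hypothesis b is also made by a team that knows the arm and supports the app, and the Discussion does not say so.

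A reader might go further and infer that the trial loses its only evidence that an effect is not expectation. The documents do not support that. Masked processing would remove analyst bias only, and participant expectation would remain in both outcomes. The primary outcome is a questionnaire score that this masking cannot reach, and its test and sample size are unchanged.

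The actual size of the bias is unknown. The conclusion on EEG rests on reading the waiver as it is worded, without exceptions, and on processing that leaves some room for discretion.

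**What to change.** Replace the general waiver in section 2.8 by a statement for each role:

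1. Participants, parents and app-support staff are not blinded.
2. EEG files are given a code that hides arm and visit. Preprocessing and score extraction are completed and locked before the code is opened.
3. Where staffing allows, the post-intervention interview is done by an existing team member who had no part in that family's app support, and any disclosure of arm is recorded. Where staffing does not allow it, the Discussion lists the unmasked clinician rating as a limitation, next to the participant effects already named there.

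The cost of item 2 is minor file handling on data that are already pseudonymised. The cost of item 3 depends on staffing that the article does not describe, hence the alternative. Neither item changes the sample size, the visit schedule or the primary analysis.
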